### Ethical Considerations

The MISBAIR trial has ethical and governance approval from Mercy Health Human Research Ethics Committee (HREC, No. R12-28) and Royal Children’s Hospital (RCH) HREC (HREC No. 33025). Informed consent to participate in the study and to share dental data to validate and develop intraoral scanning technology for dental health assessment was obtained from participants' parents or guardians. Participant records sourced have a unique identifier and are not reidentifiable to the dental team. This diagnostic agreement study has ethical approval from the RCH HREC (RCH HREC No. 88321). It will be conducted according to the principles outlined in the Declaration of Helsinki. This protocol has registration with the Australian New Zealand Clinical Trials Registry (ANZCTR; registration ACTRN12622001237774p).

## Results

As of October 2023, automated caries scoring of primary molar occlusal surfaces on the 3D models for 213 eligible participants has been completed. Data are currently being analyzed, with expected results to be published within 6 months’ time. On-screen assessment of 3D models based on color and fluorescence has commenced and is expected to be completed in March 2024, with results disseminated by December 2024.

The results of this study will be reported per the Guidelines for Reporting Reliability and Agreement Studies [37].

## Discussion

This protocol aims to fill a knowledge gap by describing an approach for determining the diagnostic agreement between VE using ICDAS and on-screen assessment of 3D models featuring fluorescence obtained with an IOS.

Intraoral scanning is increasingly being adopted in dentistry as it offers improved clinical workflows for patient assessment and treatment planning, particularly in the disciplines of prosthodontics, orthodontics, and periodontics [13,38,39]. The role of scanning technology in supporting clinical diagnostics is an emerging research area [19,20,40-43]. There is paucity in the literature describing on-screen assessment of 3D models as a method for caries detection.

A strength of our study is the consideration of different approaches to analyze agreement. Our use of multilevel generalized linear regression models to analyze surface-level dental caries data has several strengths. First, caries from the same individual are more correlated than those between individuals. If this clustering is ignored, the estimated variance may be misleadingly small [44]. We will use multilevel models that account for clustering. Second, the multilevel regression approach allows for estimating method agreement while accounting for variability due to the influence of the rater and timing of assessment [45]. Finally, because all eligible primary teeth surfaces will be analyzed the high proportion of sound surfaces will result in zero-inflated outcome data. We will address this by fitting a generalized linear regression framework allowing the use of a zero-inflated binomial distribution; whereas traditional agreement methods, such as the κ statistic, are limited in this context [46]. A limitation of the statistical approach is that the coefficient estimates derived from the multilevel model do not quantify absolute agreement. As an alternative analysis, we will analyze the total caries at the individual level with a regression-based Bland-Altman agreement analysis [36]. The excess of zeros and, hence, the nonnormal distribution of the data precludes the calculation of the limit of agreement estimates that are clinically interpretable. Consequently, we will use the intraclass correlation coefficient derived from a multilevel model fitted with a zero-inflated Poisson distribution, acknowledging that this is influenced by the variability in the population.

Further limitations include the retrospective study design, as multiple raters did not undertake VE over multiple time points, so we cannot account for the effects of this in the analysis. The prospective design of the onscreen assessment is a strength, as it has been designed to capture these effects.

The study results will inform whether 3D models can be used interchangeably with VE for detecting and classifying dental caries. This work serves as a proof of concept for performing dental examinations digitally. Study outcomes may change existing practices for data collection in children for epidemiological research. The findings may also provide insight into how scanners can be used more broadly in the provision of teledentistry services and to improve the access of young children to comprehensive dental examinations.

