### Sample Size

This is a retrospective study drawing all eligible participants from the MISBAIR trial who underwent the dental assessment at their 5-year-old study visit.

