### Statistical Analysis

Data checking and cleaning will take place before analysis. Descriptive statistics for patient characteristics such as age, sex, caries prevalence, and the proportion of children with enamel defects will be reported. The total number of tooth sites included in the analysis will be reported.

Descriptive characteristics for the rater population will be reported, including qualification, clinical background, years of experience, and training results for each rater. Interrater and intrarater reliability for on-screen assessment of 3D models based on color and fluorescence using the intraclass correlation coefficient will be reported for all examiners. These estimates will be obtained from a multilevel model fitted to the surface-level data, accounting clustering (see below), and zero inflation.

To assess agreement among methods, we will undertake both surface-level and individual-level analyses. At the surface level, caries data naturally have 3 levels with surfaces clustered within a tooth, which are clustered within an individual. Therefore, for this analysis, we will use multilevel logistic regression to estimate method agreement while accounting for clustering for the tooth. Specifically, separate multilevel models will be fitted to compare VE with each of the alternative methods by including the variable method (VE vs on-screen assessment of 3D models in approximate natural colors, on-screen assessment of 3D models in approximate natural colors featuring fluorescence, and automated system) as the fixed effect. The coefficient estimates for the variable method will be used to indicate the level of agreement. The multilevel model will be fitted with a zero-inflated binomial distribution.

At the individual level, a numerical variable representing the number of lesions per individual will be generated and analyzed with 2 approaches. First, Bland-Altman method agreement analysis will be performed using a regression approach. Specifically, a model will be constructed to regress the difference between each pair of methods on their average [36]. The analysis will be repeated for each possible pair of methods. Second, for each possible pair of methods, an intraclass correlation coefficient will be estimated from a multilevel model fitted to the paired data consisting of the 2 measures for each individual obtained from the 2 methods, fitted with a zero-inflated Poisson distribution.

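### Nonnormal lesion counts do not rule out limits of agreement, and without them no planned result says how many lesions apart two methods can be for one child

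*Protocol article*

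**What the plan says.** Under Statistical Analysis, "a numerical variable representing the number of lesions per individual will be generated and analyzed with 2 approaches". In the first, a regression form of Bland-Altman, "a model will be constructed to regress the difference between each pair of methods on their average", for every pair of methods. The second is an intraclass correlation coefficient (ICC) for every pair, from a multilevel zero-inflated Poisson model.

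The Discussion gives the reasoning. It concedes that the surface-level coefficients do not measure absolute agreement and presents the individual-level analysis as the alternative. It then states that the surplus of zeros, which makes the data nonnormal, "precludes the calculation of the limit of agreement estimates that are clinically interpretable". In place of such limits, "we will use the intraclass correlation coefficient derived from a multilevel model fitted with a zero-inflated Poisson distribution". The authors attach a caveat to that coefficient, "acknowledging that this is influenced by the variability in the population". The Discussion closes by saying that the results will inform whether 3D models and visual examination are interchangeable.

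The article names no test of the slope or intercept, no standard error, no significance level and no acceptable difference.

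**The concern.** The sentence that excludes limits of agreement gives one reason, nonnormality from excess zeros. Normality is needed only for the mean ± 1.96 SD form, and there it concerns the differences, not the counts. Percentile limits do not need it.

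The exclusion matters because of what is left: surface-level coefficients, a slope and intercept, and an ICC. None is a statement in lesions about one child. A reader deciding whether an on-screen score can replace a visual examination has to know how far apart the two may be for a given child. This is a stated exclusion, not a detail left to a fuller plan, so an analysis plan consistent with the article would carry it forward.

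**Working it through.** The protocol gives no figure to reproduce on this point. It gives 213 participants with completed automated scoring (Results), taken here as n for every pair of methods. Everything else about the data is assumed, because the article reports no zero share, mean, dispersion or error rate.

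**1. What the regression can see.** Let methods 1 and 2 have variances V1 and V2 and covariance C, with D the difference and A the average.

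- cov(D, A) = (V1 − V2)/2 and var(A) = (V1 + V2 + 2C)/4
- slope = cov(D, A)/var(A) = 2(V1 − V2)/(V1 + V2 + 2C)
- var(D) = V1 + V2 − 2C

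If V1 = V2 the slope is 0 for any C. The scatter var(D) depends strongly on C. Slope and intercept therefore carry bias, not scatter.

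**2. Numbers for an assumed population.** Half of the children have no lesions. The rest follow a negative binomial with mean 4 and shape 1. The true count then has mean 0.5 × 4 = 2 and variance 0.5 × (4 + 16 + 16) − 4 = 14. Each method detects each lesion with a given sensitivity and adds Poisson false calls. With sensitivity 0.8 and 0.2 false calls per child:

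- V = 0.64 × 14 + 0.16 × 2 + 0.2 = 9.48
- C = 0.64 × 14 = 8.96 when both methods score the same child, and 0 when the scores are unrelated

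| Case | Slope (formula) | Simulated slope, intercept | 1.96 × SD of D (formula) | Simulated |
|---|---|---|---|---|
| Two equally good methods | 0 | -0.001, 0.002 | 1.96 × √1.04 = 2.0 | 1.99 |
| Unrelated scores, same distribution | 0 | -0.001, 0.001 | 1.96 × √18.96 = 8.5 | 8.47 |
| Sensitivity 0.8 vs 0.6 | 2(9.48 − 5.72)/(9.48 + 5.72 + 13.44) = 0.263 | 0.263, -0.019 | 1.96 × √1.76 = 2.6 | 2.59 |
| False calls 0.2 vs 0.6 | 2(9.48 − 9.88)/(9.48 + 9.88 + 17.92) = -0.021 | -0.021, -0.357 | 1.96 × √1.44 = 2.4 | 2.35 |

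The first two rows cannot be told apart by slope and intercept, yet individual differences are about four times wider in the second. The last two rows show that the regression does find proportional and fixed bias.

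**3. What the ICC adds.** An ordinary ICC for two equal-variance methods is C/V: 8.96/9.48 = 0.95 in row 1 and 0 in row 2. It would separate them, but not in lesions, and it moves with the population. With var(D) held at 1.04 and V halved to 4.74, it falls to 1 − 0.52/4.74 = 0.89, although the differences are as large as before. The zero-inflated Poisson version was not evaluated.

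**4. Are limits available on zero-heavy counts?** Ten scenarios with 38% to 85% zeros were simulated, with n = 213 and 1,000 runs each, and coverage was checked in 5,000 new children per run.

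| Limits | Coverage of new differences (nominal 95%) |
|---|---|
| 2.5th/97.5th percentiles | 95.5% to 98.5% |
| Mean ± 1.96 SD | 91.2% to 95.1% |

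Both can be computed. The percentile form held its coverage throughout.

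**5. Precision.** 213 × 0.025 = 5.3, so about five children lie beyond each percentile limit.

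**6. If the slope is tested.** With two equal methods, 4,000 runs and an assumed two-sided 5% level, the constant-variance least-squares slope test rejected in 22% to 67% of runs in the nine zero-heavy scenarios where spread grows with the count. It rejected in 9.8% where error size was about constant, and in 6.1% with 2% zeros. HC3 robust standard errors gave 5.4% to 10.7% in the ten zero-heavy scenarios. The intercept test was not inflated there (0.8% to 3.1%).

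**The case against.** The Discussion does not say that limits cannot be computed. It says that interpretable ones cannot, and there is substance in that: when many children score zero by both methods, pooled limits mainly describe children without lesions. This stands as a reason to report lesion-bearing children separately. It does not support the reason given, which is nonnormality. The imprecision of the tails also stands, and calls for confidence intervals rather than omission.

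Three stronger readings are tempting, and the document does not support them.

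- A reader might infer that the regression cannot show disagreement at all. It shows fixed and proportional bias: sensitivity 0.8 against 0.6 was detected in 99.9% of runs (97.5% with HC3). It misses only random scatter.
- A reader might infer that nothing but the regression is kept. A per-pair ICC is planned as well, and an ordinary ICC would expose unrelated methods. That case is in any event an extreme illustration, since the scan follows the visual examination immediately.
- A reader might infer that the plan has a badly inflated false-positive rate. The article specifies no slope test and no constant-variance assumption, and the regression method it cites is not at hand. The rates in step 6 rest on assumed data and largely disappear with robust standard errors.

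The authors also disclose openly the limits of the surface-level coefficients and of the ICC. Disclosure does not supply the missing quantity.

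**Conclusion.** The concern holds in this form: the stated reason for excluding limits of agreement is not valid, and no output described in the article gives the size of per-child differences in lesions, which the interchangeability claim needs. The slope identity is exact. The ±2.0 and ±8.5 lesions and the coverage figures depend on the assumed populations and on n = 213, and illustrate the gap rather than predict this study's results. The behaviour of a slope test is a secondary caution that applies only if such a test is run.

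This should be fixed, but it is not a fatal flaw: no planned analysis has to be withdrawn and no data are lost.

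**What to change.** - Remove the Discussion sentence on limits of agreement, or correct it to say that the mean ± 1.96 SD form may be unsuitable for these counts.
- For each pair of methods, report the 2.5th and 97.5th percentiles of the per-child differences with bootstrap confidence intervals.
- Report the proportions of children with difference 0 and with difference within ±1 lesion. Give these and the percentile limits both overall and among children with at least one lesion by either method.
- Keep the regression of difference on average and describe it as a check for fixed and proportional bias. If its slope is tested, use robust or bootstrap intervals, because the spread is likely to grow with the count.
- Keep the ICC as a secondary, population-dependent summary.

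The cost is plan wording and minor programming on data already planned. The drawback is imprecise percentile limits, more so in the lesion-bearing subgroup, so the intervals have to be shown.

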**Methods:**

The study sample will be drawn from eligible participants in a randomized controlled trial at the Royal Children’s Hospital, Melbourne, Australia, where a dental assessment was conducted, including VE using the International Caries Detection and Assessment System (ICDAS) and intraoral scan using the TRIOS 4 (3Shape TRIOS A/S). Participant clinical records will be collected, and all records meeting eligibility criteria will be subject to an on-screen assessment of 3D models by 4 dental practitioners. First, all primary tooth surfaces will be examined for caries based on 3D geometry and color, using a merged ICDAS index. Second, the on-screen assessment of 3D models will include fluorescence, where caries will be classified using a merged ICDAS index that has been modified to incorporate fluorescence criteria. After 4 weeks, all examiners will repeat the on-screen assessment for all 3D models. Finally, an automated caries scoring system will be used to classify caries on primary occlusal surfaces. The agreement in the total number of caries detected per person between methods will be assessed using a Bland-Altman analysis and intraclass correlation coefficients. At a tooth surface level, agreement between methods will be estimated using multilevel models to account for the clustering of dental data.

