Recent advances have seen the development of computational methods as a more objective measure to quantify dental caries and support clinical diagnosis. TRIOS has developed an automated caries scoring system for their software that can automatically classify caries on occlusal surfaces based on color and fluorescence changes (TRIOS Patient Monitoring [TPM]; version 2.3; 3Shape TRIOS A/S) [16]. When comparing the diagnostic performance as quantified by the area under the curve (AUC), early in vitro and in vivo validation studies suggest that the automated score is comparable to VE at the early (AUC VE 0.71 vs 0.76) and moderate disease thresholds (AUC VE 0.90 vs 0.90), based on a histological reference standard for permanent teeth [20]. A separate investigation into the validity of this algorithm in primary teeth concluded it had comparable performance (AUC 0.88) to VE (AUC 0.96) for caries detection of primary tooth occlusal surfaces [21]. The latter was a small in vitro feasibility study; consequently, results should be interpreted cautiously and not generalized to the clinical setting. The in vivo performance of automated assessment of 3D models for caries detection in primary teeth has yet to be established.

One of the problems with investigating early caries detection methods in realistic settings is the choice of a reference standard for method comparison, as histological or operative references are rarely feasible or ethical. It is argued that when VE alone is used as a gold standard, measures of diagnostic accuracy (sensitivity and specificity) may overestimate the true accuracy of the caries detection method under investigation [22,23]. Instead, reporting on the diagnostic agreement has been suggested to be more appropriate. Diagnostic agreement quantifies the similarity between methods in detecting the outcome of interest to be used interchangeably [24].

This study describes the protocol and statistical analysis plan for determining the diagnostic agreement between VE, on-screen, and automated caries detection methods using 3D models in children.

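### The plan aims at an interchangeability statement without fixing which agreement measure, VE contrast or value supports it, and it reads agreement from a method coefficient that shows only a difference in detection rate

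*Protocol article*

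**What the plan says.** The conclusion in view is stated in the Discussion: "The study results will inform whether 3D models can be used interchangeably with VE for detecting and classifying dental caries".

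The Statistical Analysis section says "To assess agreement among methods, we will undertake both surface-level and individual-level analyses". It then sets out three measures:

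- **Surface level.** Multilevel logistic models compare VE with each alternative method. "The coefficient estimates for the variable method will be used to indicate the level of agreement".
- **Child level, Bland-Altman.** On lesion counts per child, "a model will be constructed to regress the difference between each pair of methods on their average", for every pair of methods.
- **Child level, ICC.** For every pair of methods, "an intraclass correlation coefficient will be estimated from a multilevel model fitted to the paired data" with a zero-inflated Poisson distribution.

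The Discussion limits each measure. It says that the coefficients do not quantify absolute agreement, that clinically interpretable limits of agreement cannot be obtained, and that the ICC depends on how variable the population is.

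Some structure is fixed. The objectives are numbered, initial caries is the main detection threshold (Outcome Measures), and the moderate and extensive thresholds are sensitivity analyses. The article also presents itself as more than a protocol summary: "This study describes the protocol and statistical analysis plan for determining the diagnostic agreement between VE, on-screen, and automated caries detection methods".

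**The concern.** No measure, VE contrast or acceptable value is tied to the interchangeability statement. Objective 1 alone contains two VE contrasts (on-screen with and without fluorescence), and Objective 2 adds the automated system.

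This goes beyond missing detail, because one rule that is written down can mislead. The Statistical Analysis section takes the method coefficient as an indicator of agreement. That coefficient compares how often each method calls a surface carious. It does not ask whether the methods call the same surfaces, or even the same children. A reader who sees a coefficient near zero and follows the plan would report agreement where there may be none. Conversely, a modest systematic excess of detections would be read as disagreement although the two methods rank and count the children almost alike.

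**Working it through.** The document gives no sample-size, alpha, margin or precision figure on this point, so there is no stated figure to reproduce.

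**1. Number of results.** Three VE contrasts (colour, colour plus fluorescence, automated) × three measures = 9 VE-based results at the main threshold. Four methods form 6 pairs, so all planned results at that threshold number 3 + 6 × 2 = 15. None is named as carrying the conclusion.

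**2. What the coefficient measures.** For one VE contrast, let n11 be the surfaces called carious by both methods, n10 those called by VE only, n01 those called by the alternative only, and n the total. The marginal form of the method coefficient is

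logit[(n11 + n01)/n] − logit[(n11 + n10)/n].

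It is zero whenever n10 = n01, whatever n11 is, including n11 = 0. Random intercepts do not change this. If each surface is read once by each method and the two totals are equal, the likelihood equations for the intercept and for method are both satisfied at a coefficient of zero. The zero-inflation part was not examined.

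Positive agreement, 2·n11/(2·n11 + n10 + n01), is zero when n11 = 0. It therefore separates cases that the coefficient cannot.

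**3. Can the three measures conflict?** This was simulated with 200 data sets per scenario.

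- From the document: 213 children (Results section).
- Assumed: 80 surfaces per child; child-level logit risk with mean −5 and SD 1.8, which leaves about 52% of children without a lesion.
- Stand-ins for the planned zero-inflated multilevel models: a marginal log odds ratio with child-clustered standard error, the slope of difference on average with robust standard error, and an absolute-agreement ICC on counts. Significance means two-sided 5%, also an assumption.

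| Scenario | Odds ratio (significant) | Bland-Altman slope (significant) | ICC | Surface kappa |
|---|---|---|---|---|
| A. Same count per child, different surfaces | 1.00 (0%) | 0.00 (0%) | 1.00 | 0.15 |
| B. Same overall prevalence, wrong children | 1.00 (0%) | 0.00 (0%) | 0.00 | 0.00 |
| C. All VE lesions found plus about 30% extra | 1.31 (100%) | 0.27 (99%) | 0.95 | 0.86 |
| D. 40% of VE lesions missed, as many false calls added | 1.00 (0%) | −0.47 (100%) | 0.83 | 0.59 |

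**4. Check by hand.**

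- In C, a child with a VE lesions has a difference of about 0.3a and an average of about 1.15a. The slope is 0.3/1.15 = 0.26, close to the simulated 0.27. Positive agreement is 2/(1 + 1.3) = 0.87.
- In D, the difference falls by 0.4 per VE lesion while the average rises by 0.8. The slope is about −0.4/0.8 = −0.5, close to −0.47. Positive agreement is (2 × 0.6)/(1 + 1) = 0.60.

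**5. Reading the table.** In B, C and D the same data look favourable on one measure and unfavourable on another. In A all three planned measures look perfect while agreement surface by surface is poor. Choosing one of the three would therefore not by itself support a claim about tooth surfaces, which is what Objective 1 concerns.

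**The case against.** The strongest defence is that this is an estimation study. The Discussion says that results will inform the question and calls the work a proof of concept. The objectives are to determine and compare agreement, and there is no hypothesis test. The three measures are presented as complementary, with their limits disclosed and a rationale for each addition. Most of that stands. It does not answer the use of the coefficient as an agreement indicator, or the lack of any link from the measures to the interchangeability statement.

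Several stronger readings are tempting, but the documents do not support them:

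- **That the study commits to a yes/no verdict.** The wording is softer than that.
- **That the many results inflate a false-positive rate.** The plan states no alpha and no tests, and an ICC has no null hypothesis here. A family-wise error rate would describe a procedure the plan does not contain.
- **That the measures usually disagree.** The simulations rest on assumed lesion patterns, simplified models and reading rules that are not in the document. They show only that conflict is possible.
- **That the text contradicts itself on which level leads.** The abstract says "The agreement in the total number of caries detected per person between methods will be assessed using a Bland-Altman analysis and intraclass correlation coefficients", and the Discussion says "As an alternative analysis, we will analyze the total caries at the individual level with a regression-based Bland-Altman agreement analysis". Order of mention in an abstract is not a ranking.
- **That the criterion will be chosen with results in view.** The Results section reports that the automated data were being analysed, but these belong to Objective 2. On-screen scoring was still unfinished.

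**Conclusion.** The point holds in limited form. No measure, VE contrast or acceptable value is tied to the interchangeability statement, and the coefficient is given a role it cannot fill. That second part follows from algebra and from the Discussion's own concession, not from simulation settings.

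The size of any conflict is illustrative. With 213 children and the assumed patterns, an odds ratio of exactly 1.00 went with an ICC anywhere from 0.00 to 1.00 (scenarios A, B and D). A 30% excess of detections was flagged in every run at an ICC of 0.95. A separate simulation assumed 60 surfaces per child and half the children caries-free. It gave the second pattern again: an excess of just under 30%, or a deficit of 18%, was flagged in essentially every run while the ICC stayed at about 0.9.

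Leaving this to another document is not a full answer, since the article says that it describes the statistical analysis plan. The choice of caries threshold is not in question.

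**What to change.** 1. **Statistical Analysis section.** Describe the method coefficient as a measure of systematic difference in detection (bias). Label it and the Bland-Altman slope supportive. State that a non-significant value of either is not evidence of agreement.
2. **Before on-screen results are seen,** name the VE contrast and the absolute-agreement measures that would support an interchangeability statement, with acceptable values for their confidence bounds:
   - Child level: the on-screen/VE ratio of mean lesion counts, with a confidence interval from resampling whole children, plus an absolute-agreement ICC on counts.
   - Surface level, because Objective 1 concerns tooth surfaces: for example positive and negative agreement with child-clustered confidence intervals.
   - State how the four examiners' two readings enter each measure.
3. **If no acceptable values are fixed,** limit the Discussion to a descriptive conclusion.

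VE versus on-screen with fluorescence is a reasonable primary contrast, because the Discussion opens by giving that pair as the protocol's aim. The Objective and Aims sections list colour with and without fluorescence side by side, so the choice is the investigators'. Automated-versus-VE results should be reported as a separate objective.

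The cost is wording, a bootstrap and one added surface-level summary, with no new data or readers. The downside is that the investigators must commit to acceptable values, and a favourable result on one supportive measure can no longer carry the claim.
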